## **6.6 Blinding**

Since the investigational vaccine is more viscous as compared to the placebo, it will not be possible to blind the study site member who administers the investigational vaccine. The pharmacy team members will also be unblinded. At the commencement of the study, the blinded investigational vaccine administrators will be identified and trained. There will be at least 2 investigational vaccine administrators at each site who have received training in the delivery of intradermal injections. The investigational vaccine administrators will not be permitted to be involved in patient assessments or management throughout the trial. Additionally they will not discuss what they believe the subject is receiving with either the subject or other staff members.

All other site staff and the subject will be blinded to the study treatment, COR-1 or placebo. Admedus Vaccines Pty Ltd and its representatives will also be blinded to the study treatment throughout the course of the study. The investigational vaccine administrator's will make every attempt to ensure that both the subject and the blinded team members do not observe the intradermal injection as this may threaten the integrity of the blind. The subject may place their forearm through a screen which blocks their view or may be asked to turn away during the injection. Similarly site staff will be instructed to not observe the administration of the investigational vaccine/placebo. This will be highlighted during the site initiation visit and throughout the study.

An unblinded monitor will perform drug accountability according to the Monitoring Plan.

The dose and injection regimen will not be blinded.

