### 3.2.3 Metabolism and pharmacokinetics

#### 3.2.4 Clinical trials of COR-1

The primary objective of the previous Phase I, single ascending dose study was to examine the safety and tolerability of a 3 dose regimen of COR-1 administered intradermally (ID) to healthy, non-HSV-2 infected sero-negative volunteers. In addition the study investigated whether COR-1 induced anti-HSV gD2 specific antibodies and/or produced a cell-mediated immune response to gD2 in this population. This dose escalation study aimed to identify an optimal dose of COR-1 required for induction of an efficacious immune response which could protect against future HSV infection.

A total of 22 subjects were enrolled in the study and received at least one dose of COR-1 vaccine. All subjects were included in the Safety Analysis. Twenty subjects received 3 doses of vaccine and were included in the Per Protocol Analysis. A total of 35 Treatment Related Adverse Events (TEAEs) were reported during the study period by 15 subjects (68.2%). A greater number of TEAEs were reported for the 1 mg COR-1 group (19 events) compared with the 10 mcg, 30 mcg, 100mcg and 300mcg COR-1 groups (between 2 and 7 events).

One SAE was reported in the 1 mg COR-1 group (clavicle fracture). This event was considered not related to the COR-1 vaccine and no action was taken with the study drug.

The most frequently reported TEAEs were classified under the following System Organ Classes (SOCs):

- Skin and subcutaneous tissue disorders (10 events reported by 3 subjects in the 1 mg COR-1 group only). Skin hyperpigmentation (at the injection site) was the only TEAE reported in this SOC.
- Nervous system disorders (7 events reported by 6 subjects). Events in this SOC were observed in all treatment groups except the 30 mcg COR-1 group

The majority of TEAEs experienced were classified as mild (30 events). Three events reported in the 1 mg COR-1 group were classified as severe. These events were related to the SAE of clavicle fracture. There were no trends identified by treatment group or severity for the TEAEs reported. The majority of TEAEs were considered not related or unlikely to be related to the COR-1 vaccine. 10 events of skin hyperpigmentation observed in the 1 mg COR-1 group were considered definitely related to the COR-1 vaccine.

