A total of 143 local ADRs were reported during the study period by 21 subjects (95.5%). The number of local ADRs reported increased with increasing dose of COR-1. Erythema and induration were the most frequently reported injection site reactions, occurring in at least one subject in each treatment group at some point during the vaccination phase. Erythema was reported more frequently in the 100 mcg, 300 mcg and 1 mg COR-1 treatment groups. Induration was reported more frequently in the 1 mg COR-1 treatment group. All injection site reactions were classified as mild in intensity.

A total of 14 systemic ADRs were reported during the study period by four subjects (18.2%). The most frequently reported were headache, fatigue, chills, malaise, pain and pyrexia. There were no trends in the frequency of systemic ADRs by treatment group. All the systemic ADRs reported were classified as mild in severity.

Review of haematology and biochemistry results revealed no trends or notable changes over time following vaccination with COR-1 at any dose level. There were no trends or notable findings in vital signs following each vaccination with COR-1 at any dose level.

A review of the safety data suggests that 3 ID vaccinations of the COR-1 vaccine at three weekly intervals were safe and well tolerated.

No anti-HSV gD2 antibodies were detected in any subject by ELISA, indicating that no subjects had seroconverted to COR-1 during the study based on the utilised method.

IFN- $\gamma$  production by T cells specific for gD2 antigen was induced in 19 of the 20 subjects who completed the study as planned and was considered a cell-mediated response to the COR-1 vaccine. The response rates were similar in all treatment groups with 100.0% of subjects responding to the COR-1 vaccine in the 10 mcg, 30 mcg, 300 mcg and 1 mg groups and 75.0% responding in the 100 mcg group.

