## 4.3 Study Design

This is a randomized single or multi centre, double blind, placebo-controlled, parallel group pilot study to assess the safety and efficacy of a therapeutic HSV-2 DNA vaccine in HSV-2 positive adults. Subjects will be randomized to receive either COR-1 or placebo using a 3:1 allocation ratio. Treatment assignment to either COR-1 or placebo will be double-blinded. There will be 2 Groups of subjects. Group 1 will receive one injection into each forearm. Once this group has been fully allocated, Group 2 will commence recruitment. Group 2 will receive two injections to the one forearm.

There are two primary reasons for inclusion of the 2 placebo arms:

- To maintain the blind; and
- To describe any natural variation in viral shedding rates between the baseline shedding assessment pre- and post-administration of the placebo.

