### 6.4.2 Physical examination

A complete physical examination (including head, ears, nose, throat, lungs, lymph nodes, heart, abdomen, skin and genital region) will be conducted to determine study eligibility at screening. A symptom directed physical examination will be performed at subsequent visits as defined in Section 6.3. The symptom directed physical examinations will be performed based on signs and symptom the subject has reported verbally and/or documented in the diary booklets. A symptom directed physical examination may also be performed if in the opinion of the Investigator it is required.

Prior to each injection, the forearm that is to be injected will be examined and findings from this examination will be documented.

At each visit, following Visit 5, the subject's injection sites will be inspected and any reactions will be graded. Please refer to Section 8. Any reactions should also be captured as adverse events within the CRF.

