#### 6.4.11 Punch biopsies

The vaccine has been demonstrated to produce a reddened thickening at the site of administration which appears after 24 hours and is maximal at 48 hours. This is characteristic of a delayed type hypersensitivity reaction, which would indicate induction of an appropriate antigen specific cell mediated immune response. However, it could represent some other vaccine induced non-specific or inflammatory response. To establish the nature of the response, immunohistochemistry of the lesion at 48 hours may provide evidence of a T-cell infiltrate, oedema and or a neutrophilic infiltrate which would not be associated with antigen specific immunity).

All subjects who provide written informed consent at Screening will have a skin biopsy taken from the injections site area at Visit 10 for immunohistochemical analysis to assist in determining the type of immune response occurring.

Please refer to Appendix 2 for further information.

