## 6.8 Formulation

### 6.8.1 Investigational products

Admedus' HSV vaccine (COR-1) is a 1:1 mixture of two DNA plasmids. Both plasmids comprise the Nature Technology Corporation (NTC) expression vector NTC8485 minus the enhanced green fluorescent protein sequence. The first has a codon optimised DNA sequence insert encoding full length glycoprotein D from HSV-2 (gD2) (named NTC8485-O2-gD2) and the other with a codon optimised DNA sequence insert encoding one ubiquitin repeat fused to the N-terminal end of amino acids 25-331 of truncated gD2 (named NTC8485-O2-Ubi-gD2tr). In summary:

1. COR-1A: plasmid DNA NTC8485-O2-gD2
2. COR-1B: plasmid DNA NTC8485-O2-UgD2tr

It is formulated in sterile, isotonic and endotoxin free Tris (hydroxymethyl) amino methane hydrochloric acid and Ethylenediaminetetraacetic acid (EDTA) at pH 8 (TE buffer). Placebo vaccine is sterile, isotonic and endotoxin free TE buffer.

Each COR-1 single use vial contains 1,250 mcg in 0.5mL

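### The blind of the subject and the Investigator is at serious risk: section 6.6 hides the injection but not the local reaction that COR-1 is described as producing

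*Protocol*

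**What the plan says.** Section 4.3 introduces its rationale with "There are two primary reasons for inclusion of the 2 placebo arms", and the first reason listed is maintaining the blind. Section 6.6 says that "All other site staff and the subject will be blinded to the study treatment, COR-1 or placebo". It accepts that the administrator and pharmacy are unblinded because COR-1 is more viscous. It then keeps administrators out of assessments and silent about treatment, and has the subject and other staff not watch the injection. Nothing in it addresses what is visible afterwards.

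On the active product, section 6.4.11 describes COR-1 as "demonstrated to produce a reddened thickening at the site of administration which appears after 24 hours and is maximal at 48 hours". Section 3.2.4 reports Phase I: "A total of 22 subjects were enrolled in the study and received at least one dose of COR-1 vaccine", and "A total of 143 local ADRs were reported during the study period by 21 subjects (95.5"%). It adds that "The number of local ADRs reported increased with increasing dose of COR-1", that erythema and induration were the most frequent reactions, and that all injection site reactions were mild. Injection-site hyperpigmentation was seen only at 1 mg, in 3 subjects. The present trial gives 2 x 500 mcg, or 1 mg, per vaccination (section 4.4).

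On the control, section 6.8.1 says "Placebo vaccine is sterile, isotonic and endotoxin free TE buffer". No reaction rate for it is given.

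On who sees and who judges:
- The subject measures reactions with a ruler for 7 days after each vaccination (section 6.4.10).
- After Visit 5, at each visit "injection sites will be inspected and any reactions will be graded" (section 6.4.2). At Visit 10, about 48 hours after the third dose, every subject's sites are assessed and photographed (section 6.3.2.4).
- The Investigator assigns the severity and relationship of adverse events (section 8.2.1).
- The Investigator or designee decides whether a lesion fits genital HSV-2. The outbreak definition is by appearance alone, although swabs go to the central laboratory (section 8.11).

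**The concern.** The precautions in section 6.6 deal with the smaller cue, viscosity at the moment of injection. The larger cue, the skin reaction over the following days, reaches both the subject and the Investigator's team, and the Protocol requires both to look at it closely. No separate site assessor and no check of the blind is described.

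The exposed outcomes depend on what a subject chooses to report or an Investigator decides: systemic reactions and vaccine-related adverse events (part of the primary endpoint, section 4.2), the number of symptomatic recurrences, and time to first recurrence. Someone who infers placebo from a quiet forearm may report more lesions; someone who infers COR-1 may report fewer lesions, or more fatigue and headache. A difference between arms could then be reporting bias rather than vaccine effect. Nothing planned would show afterwards how much unblinding occurred.

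**Working it through.** **Inputs from the Protocol.** Phase I subjects dosed: 22, all on COR-1. Subjects with any local ADR: 21 (section 3.2.4). Allocation 3:1, giving 30 COR-1 and 10 placebo (sections 4.3 and 6.5).

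**Input not in the Protocol.** The placebo reaction rate q. It is varied from 0% up to the COR-1 rate.

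**Step 1, reproduce the stated figure.** 21/22 = 95.45%, which matches the printed 95.5%. The exact (Clopper-Pearson) 95% CI is 77.2% to 99.9%.

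**Step 2, how well a reaction reveals the arm.** Let s be the COR-1 reaction rate, and take the rule that a reaction means COR-1 and no reaction means placebo.

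- Share guessed correctly = 0.75 s + 0.25 (1 − q)
- P(placebo | no reaction) = 0.25 (1 − q) / [0.25 (1 − q) + 0.75 (1 − s)]

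The benchmarks without any cue are 75% correct (always guess COR-1) and a 25% chance of placebo.

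| Assumed q | Correct, s = 21/22 | P(placebo, no reaction), s = 21/22 | Correct, s = 77.2% | P(placebo, no reaction), s = 77.2% |
|---|---|---|---|---|
| 0% | 96.6% | 88% | 82.9% | 59% |
| 10% | 94.1% | 87% | 80.4% | 57% |
| 25% | 90.3% | 85% | 76.6% | 52% |
| 40% | 86.6% | 81% | 72.9% | 47% |
| 50% | 84.1% | 79% | 70.4% | 42% |
| 75% | 77.8% | 65% | 64.1% | 27% |
| 95.5% | 72.7% | 25% | – | – |

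Worked example at s = 77.2%, q = 40%: 0.75 × 0.772 + 0.25 × 0.60 = 0.579 + 0.150 = 0.729. P(placebo | no reaction) = 0.150 / (0.150 + 0.75 × 0.228) = 0.150 / 0.321 = 0.47.

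**Step 3, break-even.** The rule beats always guessing COR-1 when 0.75 s + 0.25 (1 − q) > 0.75, that is q < 1 − 3(1 − s). At s = 21/22 this is q < 19/22 = 86.4%. At s = 77.2% it is q < 1 − 3 × 0.228 = 31.6%. Above break-even but below equal rates the reaction still carries information: in the worked example a non-reactor is on placebo with probability 47%, not 25%.

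**Step 4, expected counts.** At s = 21/22, about 30 × 1/22 = 1.4 COR-1 subjects would show no local reaction, against 10 (1 − q) placebo subjects: 9 at q = 10% and 5 at q = 50%.

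**The case against.** A reader might infer that COR-1 gives a visible reaction in about 95% of subjects, so that the placebo cannot keep the blind. The Protocol does not support that.

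- The 21 of 22 counts any local ADR, over up to three vaccinations and pooled from 10 mcg to 1 mg. For erythema and induration, section 3.2.4 says only that at least one subject in each dose group had them. The 48-hour description in section 6.4.11 carries no frequency.
- Every Phase I subject described received COR-1, so no placebo comparison exists. If buffer reacted about as often and as markedly, the cue would disappear.
- With 22 subjects the rate could be as low as 77%, and the gain from the cue is then much smaller.

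These points stand, and they are why the conclusion is that the blind is at risk rather than lost. Against them, the number of local ADRs and the size of the erythema both rose with dose, and this trial uses the top Phase I total dose. Nothing in the Protocol suggests that buffer alone produces the same thickening.

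It can also be said that the recurrence endpoints are exploratory, the analysis is descriptive (section 11), shedding is read in a laboratory and listed first among the efficacy endpoints, lesion swabs are already sent for testing, and a vehicle control properly isolates the plasmid's contribution to local reactions. All of this is fair, and no change of placebo is called for. But bias distorts a described difference as much as a tested one, and the primary endpoint includes systemic symptoms and vaccine-related events. The synopsis says clinic swabs serve to confirm the diagnosis, yet no endpoint requires a positive result. A SAP may settle which outbreaks count; the Protocol as it stands fixes a definition by appearance only.

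**Conclusion.** The concern holds as a serious and unaddressed risk to the blind of the subject and of the Investigator who grades sites, assigns causality and judges outbreaks. Section 6.6 asserts a blind that its safeguards do not secure.

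The size cannot be fixed from the Protocol. With the Phase I point estimate, the crude rule is right in about 97% of subjects at a zero placebo rate and about 73% at equal rates, against 75% without the cue. At the lower confidence limit it runs from 83% at a zero placebo rate to 70% at a 50% placebo rate. These figures assume that any local ADR acts as a cue, that the pooled Phase I rate carries over to this trial, and that q lies somewhere in the range shown. Size, duration and lasting pigmentation of a reaction could add to the cue and are not modelled.

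The outcomes affected are recurrences, systemic symptoms and causality. Centrally read shedding is much less exposed, although its swabs are collected by the subject.

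**What to change.** 1. For the recurrence count and time to first recurrence, count an outbreak in the main summary only if at least one lesion swab already collected under section 8.11 is HSV-2 positive at the central laboratory. Show all clinical outbreaks beside it. State that these lesion swabs are tested by PCR: section 8.11 names no method, and the synopsis mentions PCR or viral culture in one place and viral culture in another.
2. Record the subject's and the Investigator's treatment guess, with the reason, for example at Visits 11 and 22.
3. State that recurrence, systemic-symptom and causality results are read as potentially unblinded, with centrally read shedding as the lead efficacy measure.

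Reordering assessments within a visit would not help, because site reactions are already known from earlier visits.

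The cost is Protocol wording, the guess-and-reason questions on the CRF and, if lesion swabs were meant only for culture, PCR on swabs already taken. No additional swabs are needed. The downside is that typical but PCR-negative or unswabbed outbreaks leave the main count, though they stay in the second table. Laboratory confirmation removes false-positive outbreaks; it does not correct lesions that subjects fail to report. The treatment guesses measure unblinding but do not prevent it.

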## **6.7 Method of Unblinding**

### **6.7.1 Medical Emergency**

Code break envelopes will be provided to participating sites. The Investigator may request the treatment assignment in emergency situations only. The breaking of the blind will only be sanctioned where knowledge of the study medication treatment will affect subject management. The Investigator will discuss with the Sponsor prior to any un-blinding taking place, unless immediate knowledge of the treatment allocated is required for the Subject's care.

If the code is broken a note to file will be generated by the individual who broke the code explaining the reason and date that the blind was broken. Included in this document should be details of the person who authorised the code break, and the identity of the study product allocated to the subject. This must be countersigned by the Investigator.

Reason(s) for un-blinding will be clearly documented and the details included in the study report.

### **6.7.2 End of Study**

The randomisation code will be broken by the Study Statistician once data entry has been completed, the database locked, and the per-protocol population for analysis established and the Statistical Analysis Plan (SAP) finalised and approved. Admedus Vaccines Pty Ltd will provide written permission to the Study Statistician prior to the breaking of the randomisation code.

## 6.8 Formulation

### 6.8.1 Investigational products

Admedus' HSV vaccine (COR-1) is a 1:1 mixture of two DNA plasmids. Both plasmids comprise the Nature Technology Corporation (NTC) expression vector NTC8485 minus the enhanced green fluorescent protein sequence. The first has a codon optimised DNA sequence insert encoding full length glycoprotein D from HSV-2 (gD2) (named NTC8485-O2-gD2) and the other with a codon optimised DNA sequence insert encoding one ubiquitin repeat fused to the N-terminal end of amino acids 25-331 of truncated gD2 (named NTC8485-O2-Ubi-gD2tr). In summary:

1. COR-1A: plasmid DNA NTC8485-O2-gD2
2. COR-1B: plasmid DNA NTC8485-O2-UgD2tr

It is formulated in sterile, isotonic and endotoxin free Tris (hydroxymethyl) amino methane hydrochloric acid and Ethylenediaminetetraacetic acid (EDTA) at pH 8 (TE buffer). Placebo vaccine is sterile, isotonic and endotoxin free TE buffer.

Each COR-1 single use vial contains 1,250 mcg in 0.5mL

**Table 5: Investigational Products**

| Name:                      | COR-1                                                                                |
|-----------------------------------|---------------------------------------------------------------------------------------------|
| Characteristics & Physical State: | Clear, colourless solution free from visible particulate matter containing 500 mcg of COR-1 |
| Supplied by:                      | VGXI Inc. (The Woodlands, Texas, USA)                                                       |
| Storage Conditions:               | Store at minus 20 degrees Celsius +/- 5 degrees                                             |
| Package                           | 2 mL clear vial                                                                             |
| Name:                      | Placebo                                                                              |
| Characteristics & Physical State: | Clear, colourless solution free from visible particulate matter containing TE buffer.       |
| Supplied by:                      | Sypharma Pty Ltd. ([name])                                  |
| Storage Conditions:               | Store at 20 degrees Celsius +/- 5 degrees                                                   |
| Package                           | 2 mL clear vial                                                                             |

Please refer to the IB and Certificate of Analysis (CoA).

### 6.8.2 Supply, packaging and labelling, storage and handling

COR-1 will be manufactured under the current Good Manufacturing Practice (cGMP) conditions by VGXI Inc. [name] under licence from Admedus Vaccines.

The batch number, expiry date and documented compliance with specification results will be included in the COR-1 certificate of analysis. Evidence of cGMP will also be made available. The vaccine will be supplied to the study site after receipt of required documents in accordance with the Sponsor authorised release procedures. Clinical trial labels will comply with Annex 13 of the Australian Code

of Good Manufacturing Practice for Medicinal Products – Manufacture of Investigational Medicinal Products.

COR-1 must be stored in a secure area with access limited to the pharmacist and authorized staff. The vials and outer packaging will be stored frozen at  $-20 \pm 5^{\circ}\text{C}$ , and thawed to room temperature prior to use. The COR-1 vials contain 1,250mcg per 0.5 mL.

The clinical study personnel must maintain a temperature log for the freezer which houses the investigational product. Daily minimum and maximum temperatures will be recorded in the temperature logs.

The packaging lot numbers will be recorded on the investigational product accountability record.

The pharmacy team will be unblinded to the subject treatment allocation. There will be an unblinded monitor who will perform IP accountability/reconciliation.

Refer to the Pharmacy Manual for detailed information regarding the storage, preparation and administration of COR-1.

At a minimum, the immediate packaging should include the following information:

- Sponsor name;
- Protocol number;
- Name/drug code;
- Dose/product strength;
- Batch number or batch identifier (in case of double blind studies);
- Subject ID; and
- Dosage form.

